## Abstract

**Background:**

In August 2010, the Federal Joint Committee (G-BA) decided that negative pressure wound therapy (NPWT) would not be reimbursable in German ambulatory care. This decision was based on reports from the Institute for Quality and Efficiency in Health Care (IQWiG), which concluded that there is no convincing evidence in favor of NPWT. The aim of this diabetic foot study (DiaFu study) is to evaluate whether the clinical, safety and economic results of NPWT are superior to the results of standard wound treatment.

**Methods/Design:**

The DiaFu study is designed as a national, multicenter, randomized controlled clinical superiority trial with a special focus on outpatient care in Germany. Competent patients in inpatient and outpatient care suffering from a chronic diabetic foot wound for a minimum of four weeks may be included in the study. The trial evaluates the treatment outcome of the application of a technical medical device which is based on the principle of NPWT (intervention group) in comparison to standard moist wound therapy (control group). All treatment systems used in the intervention group bear the symbol of free trade capacity in the European Union (CE mark) and will be operated within normal conditions of clinical routine and according to manufacturer’s instructions. Primary endpoints are the time to complete wound healing and the rate of wound healing achieved in each group within the maximum study treatment time of 16 weeks. Primary endpoints will be confirmed by blinded assessment of wound photographs.

**Discussion:**

The DiaFu study will provide solid evidence regarding the efficacy and effectiveness of NPWT until 31 December 2014, the date when G-BA plans to decide on future reimbursement of NPWT in both ambulatory and in-hospital care. The study is designed to comply with all quality requirements of G-BA and IQWiG and will contribute to evidence-based wound care in Germany. The study has been initiated by the statutory health insurance companies in Germany and is co-funded by two manufacturers of NPWT systems.

**Trial registration:**

Clinical Trials.gov registration number: NCT01480362 (date of registration: 23 November 2011).

German Clinical Trials Register number: DRKS00003347 (date of registration: 22 November 2011).

## Background

### Diabetes and diabetic foot wounds

Diabetes mellitus (DM) is a prevalent global chronic disease and describes a metabolic disorder. It is characterized by chronic hyperglycemia and disturbances in carbohydrate, fat and protein metabolism. These disturbances result from an inability of the pancreas to produce enough insulin, the body’s inability for an effective use of the produced hormone, or both.

The World Health Organization (WHO) estimates that more than 180 million people worldwide suffer from diabetes [1]. Even higher numbers have been predicted by the International Diabetes Federation (IDF), who reported in 2003 that 194 million adults were diagnosed with diabetes [2]. Both organizations estimate that in 2030 the number of those diagnosed will have almost doubled, mainly due to demographic changes [3]. Diabetes management involves a variety of costs and imposes enormous resource burdens, both on the individual and on healthcare systems. Diabetes and its sequelae cause significant economic consequences on individuals, families, health systems and countries. The WHO has estimated that 2.5 to 15% of annual national healthcare budgets are spent on diabetes-related illness alone [1].

The Diabetic foot wound is a common and frequent secondary syndrome that can lead to amputation. Due to arterial abnormalities and diabetic neuropathy, as well as a tendency to delay wound healing, infection or gangrene of the foot may develop. Acute and chronic wounds with healing impairment are a common problem of healthcare [4]. Complications associated with non-healing wounds range from inconvenient to life threatening and can be more common and serious than those related to the underlying disease. The occurrence of impaired wound-healing represents a multi-disciplinary treatment and cost-intensive clinical problem whether it is caused by infectious or non-infectious reasons.

### Modern wound treatment and negative pressure wound therapy

Modern wound treatment concepts include different types of moist dressings and topical agents, although only a few of these treatments have been convincingly shown to give higher wound closure rates compared with traditional wet gauze dressings [5, 6].

Negative pressure wound therapy (NPWT) was developed at the Wake Forest University (Winston-Salem, North Carolina) in the early 1990s [7, 8]. NPWT consists of an open-cell foam dressing covered with an adhesive drape. The dressing is connected to a vacuum pump that creates and maintains a sub-atmospheric pressure (intermittent or continuous). Positive effects of NPWT on wound healing have been demonstrated in basic studies [8, 9], and many case reports and case series document a broad use of NPWT in various clinical settings.

### Recent history of NPWT - clear evidence is still missing

In 2004 the German Federal Joint Committee (Gemeinsamer Bundesausschuss (G-BA)) commissioned an analysis of the available studies regarding NPWT to the Institute for Quality and Efficiency in Healthcare (Institut für Qualität und Wirtschaftlichkeit im Gesundheitswesen (IQWiG)) to support decision-making on the reimbursement of NPWT by the German statutory health insurance funds. The G-BA is the legislative institution of the German healthcare self-administration system. The IQWiG is an independent non-profit and non-government scientific institute that receives commissions from the Federal Joint Committee and the German Ministry of Health. The performed analysis aimed to evaluate the clinical benefit of NPWT in comparison with conventional forms of wound care, and to compare the benefit of various forms of NPWT for acute and chronic wounds with regard to patient-relevant outcomes on the basis of the published literature. The systematic examination of the clinical effectiveness and safety of NPWT compared with conventional wound therapy concluded that although there is some indication that NPWT may improve wound healing, the body of evidence available is insufficient to clearly prove an additional clinical benefit of NPWT. In addition, the large number of prematurely terminated and unpublished trials has been a reason for concern [10–12]. A 2007 Cochrane review concluded that trials comparing topical negative pressure (TNP) with alternative treatments for chronic wounds have methodological flaws and data do demonstrate a beneficial effect of TNP on wound healing. However, further better quality research is needed [13]. In 2011 Peinemann and Sauerland updated the systematic literature review [14] and concluded that although there may be a positive effect of NPWT, a clear evidence that wounds heal any better or worse with NPWT than with conventional treatment is still missing and better RCTs are still needed to evaluate NPWT. A Cochrane intervention review performed in 2013 concluded that there is some evidence to suggest that NPWT is more effective in healing post-operative foot wounds and ulcers of the foot in people with DM compared with moist wound dressings. However, these findings are uncertain due to the possible risk of bias in the original studies [15]. Therefore it can be concluded that current RCT evidence is limited and further trials are required to reduce uncertainty around decision-making regarding the use of NPWT to treat foot wounds in people with DM.

### Aim of the DiaFu study

This RCT is designed to prove that NPWT therapy leads more frequent and earlier to complete healing of diabetic foot wounds as compared to conventional moist wound therapy. Furthermore, it aims to show that NPWT therapy is also safe and effective when provided in an ambulatory care setting and to prove its overall cost-effectiveness. This trial is designed to comply with all quality requirements (randomized trial, low potential for bias; see Discussion section) of IQWiG and G-BA, as well as other European authorities.

## Methods/Design

The DiaFu study is designed as a national, multicenter, randomized controlled clinical superiority trial across Germany, with blinded photographic analysis of the primary endpoint. Participants are randomly allocated in a 1:1 ratio to each treatment group. Allocation to treatment groups is performed using a centralized web-based tool. To ensure good balance of participant characteristics in each group a stratified randomization is performed. Participants are stratified by study centre and by Wagner-Armstrong stage within each centre (<Wagner-Armstrong stage 2C and ≥ Wagner-Armstrong stage 2C; Figure 1). Due to the physical differences between the treatment regimens it is not possible to blind either participant or physician to the treatment arm. To address issues of blinding, confirmation of wound closure will be assessed via blinded assessment of wound photographs by independent observers.

**Figure 1 Fig1:**
[figure not shown]
**Stratification of DiaFu study participants according to Wagner-Armstrong classification.** Participants of the DiaFu study are stratified by study center and by Wagner-Armstrong stage within each center (Group 1: <Wagner-Armstrong stage 2C and Group 2: ≥Wagner-Armstrong stage 2C). The table shows the modified Wagner-Armstrong classification scheme. Strata-Group 1 is marked blue and Strata-Group 2 is marked red.

### Phase and classification of the trial

The study is classified as an examination of the clinical application of CE-marked medical devices with risk category 2b (increased methodical risk) according to risk classification rules based on the annex IX of the European Union (EU) Directive 93/42 / European Economic Community (EEC). According to the German Medical Device Act (MPG) the trial is classified as an exemption to clinical investigation according to paragraph 23b MPG. This is due to the fact that the investigational devices are CE-marked, will only be operated within intended use and there will be no additional invasive or otherwise straining examinations. Examination results will only be documented if collected within clinical routine. Ethical approval of the Lead Ethical Committee (LEC, German: Federführende Ethikkommission) ‘Ethical Committee of the University of Witten/Herdecke’ has been fully granted without any conditions. As the trial will be performed in accordance with paragraph 23b MPG, further participating centers in Germany will only receive a professional legal advice for the respective main clinical investigator. Ethical approval of participating centers in Germany is not applicable.

### Setting

This multicentre study will be conducted in hospital departments and/or outpatient facilities with a special qualification for diabetic foot care (Figure 2). Study therapy will be started in-hospital or in ambulatory care and should be continued in ambulatory care whenever possible. The maximum study treatment time is set as 16 weeks after randomization and initiation of therapy. Randomized wound therapy must be started no later than six hours after the last wound preparation which can either be a wound cleansing, debridement or an amputation.

**Figure 2 Fig2:**
[figure not shown]
**DiaFu study sites.** Recruitment of study patients is performed in hospitals and outpatient facilities across Germany with a specific qualification for the treatment of chronic diabetic foot wounds. The table lists all study sites ready for patient recruitment as of 25 October 2013.

If a patient requires further local wound treatment after the end of the maximum study treatment time either standard wound treatment or NPWT may be performed as estimated by the treating physician to provide optimal wound care.

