### Primary and secondary endpoints

Time until complete (100% epithelization) wound closure and the number of wound closures in each treatment group achieved in the maximum study treatment time of 16 weeks (112 days) are the primary endpoints of the DiaFu study. Complete wound closure is defined by 100% epithelialization of the wound (no granulation tissue visible), no drainage, no sewing material and no need for wound dressing or adjuvants. The assessment of complete wound closure is primarily based on the central blinded review of photographs performed by independent analyzers. Complete wound closure can be achieved either by surgery or by secondary intention. However, surgical intervention (for example wound suture, skin grafting or flap transplantation) is allowed only if the wound bed is prepared adequately. Sustainment of complete wound closure has to be proven by a satisfactory follow-up examination of the area 14 days after the intervention (wound closure verification visit). If the wound cannot be closed before the end of the maximum treatment time of 16 weeks, a study visit to assess the wound status and for evaluation of the secondary endpoints is performed.

Secondary clinical endpoints are the time until complete wound closure within the study time of six months, the number of wound closures per treatment group achieved within six months, the time until optimal preparation of the wound bed for further treatment (a minimum of 95% granulation), recurrences, amputations with incidence and extent, the wound size over time (area of wound opening, maximal length and width (cm^2^)) and the composition of wound tissue (percentage of epithelial layer, granulation tissue and fibrin).

The incidence of serious adverse events (SAEs) including mortality of any cause within six months from the time of initiation of therapy, incidence of device-related adverse events (ADEs) and incidence of wound-related adverse events (AEs) occurring within the study treatment time of 16 weeks or until wound closure confirmation are considered to be safety endpoints of this trial.

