### Health economic evaluation and analysis

In addition to the evaluation of clinical treatment effectiveness, a prospective assessment of health economic issues with a focus on the direct medical costs of wound treatment will be performed. This includes assessment of the parameters relevant for inpatient and outpatient resource use. A cost-effectiveness analysis using PRO and the number of wound closures as effectiveness measures will be performed. The economic evaluation is performed from the perspective of the German social insurance over the time horizon of the study period. To estimate costs the resource use is measured in natural units (for example duration of dressing changes in minutes). The average resource use per patient is calculated and priced with opportunity cost approximated over German market prices or schedule prices (for example wage agreements for staff costs). A sensitivity-analysis is performed by replacing the mean costs and effects with the upper and lower bound of the respective 95% confidence interval. Costs and effectiveness results are synthesized in an incremental cost-effectiveness ratio.

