### Ensuring outpatient care of study participants with NPWT

In Germany outpatient care with NPWT is not generally reimbursed. To ensure the optimal patient-centered care and to avoid any bias, the participating health insurance companies are providing integrated care contracts for NPWT in the ambulant treatment sector. Moreover, integrated care contracts are provided for the ambulant NPWT of up to 7000 patients with acute and chronic wounds in Germany.

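### After day 112 either treatment may be used in either arm, so the six-month closure results compare starting strategies, and the article plans no by-arm safety or cost contrast limited to the randomised treatment period

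*Protocol article*

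**What the plan says.** **Treatment.** The Setting section states: "The maximum study treatment time is set as 16 weeks after randomization and initiation of therapy". For a patient who still needs local wound treatment after that, the paragraph below Figure 2 says that "either standard wound treatment or NPWT may be performed as estimated by the treating physician to provide optimal wound care". This applies to both arms. The Methods/Design introduction says that neither patient nor physician is blinded.

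**Endpoints.** Both primary endpoints stop at the same point: closures and time to closure "achieved in the maximum study treatment time of 16 weeks (112 days) are the primary endpoints of the DiaFu study". The first two secondary endpoints go further: "the time until complete wound closure within the study time of six months, the number of wound closures per treatment group achieved within six months". SAEs and all-cause mortality are counted to six months from the start of therapy. Device-related and wound-related events stop at 16 weeks or at closure confirmation.

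**Analysis.** Under Statistical analysis, primary and secondary endpoints are analysed by randomised group whatever treatment was given. Safety data are grouped by the treatment actually given. The economic evaluation runs "over the time horizon of the study period", with patient-reported outcomes and number of closures as effect measures.

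**The concern.** The stated aim is to show that NPWT heals more wounds, and heals them sooner, than moist therapy, and that it is safe and cost-effective. The treatment contrast is maintained only to day 112. After that, an unblinded physician may start NPWT in a control patient or stop it in an NPWT patient. Funding is not an obvious barrier, since "integrated care contracts are provided for the ambulant NPWT of up to 7000 patients with acute and chronic wounds in Germany", although the article does not say whether those contracts cover trial participants after week 16.

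A reader of the six-month closure results could therefore take a small difference as a lost treatment effect when it partly reflects later treatment choices. Safety raises a different problem: once patients are grouped by treatment given, a switch made because a wound has not healed decides the group in which a later event is counted. The results are meant to inform a reimbursement decision, so it matters which question each of them answers.

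**Working it through.** **1. The plan's own figure.** Inputs from Power calculation: 45% against 30% closure at 16 weeks, α = 0.05 (taken as two-sided), power 80%. With pooled variance under the null hypothesis and mean rate 0.375:

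n = [1.960·√(2·0.375·0.625) + 0.842·√(0.45·0.55 + 0.30·0.70)]² / 0.15² = (1.342 + 0.569)² / 0.0225 ≈ 162.3 per group.

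The stated 162 reproduces (163 if rounded up). It concerns the 16-week endpoint and is not affected by this point.

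**2. Patients who could enter the free-choice phase.** NPWT: 0.55 × 162 = 89.1. Control: 0.70 × 162 = 113.4. Together 202.5 of 324, or 62.5%. This is an upper limit, because only those who need further local treatment are concerned.

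**3. How far later choices could move six-month closure.** Assumptions, not in the article: six months is 26 weeks, the closure hazard is constant, and the treatment in use sets the hazard after week 16.

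- Closure in weeks 16 to 26 among open wounds on standard care: 1 − 0.70^(10/16) = 20.0%
- The same on NPWT: 1 − 0.55^(10/16) = 31.2%

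Six-month closure is 45 + 55q in the NPWT arm and 30 + 70q in the control arm, with q taken from the treatment used after week 16.

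| After week 16 | NPWT arm | Control arm | Difference (points) | Power at 162 per arm |
|---|---|---|---|---|
| No switching | 62.1% | 44.0% | 18.2 | 91% |
| All open wounds on standard care | 56.0% | 44.0% | 12.0 | 58% |
| All open wounds on NPWT | 62.1% | 51.8% | 10.3 | 47% |
| Complete swap | 56.0% | 51.8% | 4.2 | 11% |

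Power is by normal approximation, two-sided 0.05. Taking six months as 183 days changes only the last difference, to 4.0. Without the hazard model, if later closure among open wounds is the same in both arms, the difference is 15 × (1 − q) points: 13.5 at q = 10% and 9.0 at q = 40%.

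**4. Cost-effectiveness ratio.** The ratio is (cost NPWT arm − cost control arm) / (closures NPWT arm − closures control arm). If the horizon is six months, control patients who switch add NPWT costs and NPWT-aided closures to the control side. In the table, moving from no switching to all on NPWT changes the denominator by a factor of 18.2/10.3 ≈ 1.8. The numerator moves too, but the article gives no cost figures, so the net change cannot be sized.

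**5. SAEs and mortality.** Take a control patient, unhealed at day 112, who then receives NPWT and dies in month five. Grouped by treatment given, this patient's group depends on a choice made after randomisation. If counted under NPWT, that group gains patients selected for not having healed and for having survived to day 112. The direction of the resulting bias cannot be predicted. Counting events to day 112 by randomised arm avoids this, and the stated endpoints include no such comparison.

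**The case against.** The strongest reply is that the six-month comparison is a sound randomised comparison. It follows the intention-to-treat principle, and comparing starting strategies under later usual care is a fair secondary question, especially for a payer. Both six-month closure endpoints also have day-112 versions, namely the primary endpoints. NPWT is described under Intervention and control as a temporary therapy to be stopped when the wound is ready for closure, so discontinuation is already part of the first 16 weeks. All of this stands. It means that the six-month closure results need the right reading, not removal.

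The size is also open to challenge. The Discussion describes stagnation and a slow start in chronic wounds, which fits constant hazards poorly, and a complete swap is an extreme case. The table gives illustrative bounds, not a forecast.

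Three stronger readings are tempting, but the article does not support them:

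- *SAEs are compared by arm to six months and so diluted.* They are not compared by arm; safety is grouped by treatment given. The weakness is loss of randomisation, not dilution.
- *The cost-effectiveness ratio is fixed at six months.* The economic section says only study period and gives no window for the closure count. Six months is a plausible inference, because the endpoint section calls six months the study time ("Secondary clinical endpoints are the time until complete wound closure within the study time of six months") and EQ5D is collected then, but it is an inference.
- *Amputations are also compared at six months.* The article gives them no window.

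The per-protocol analysis does not settle the matter. It excludes changes of wound treatment without saying whether a permitted change after week 16 counts. If it does, the analysis removes patients because they had not healed.

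**Conclusion.** The point holds in limited form. The six-month time to closure and closure count compare two starting strategies, each followed by free choice, and should not be read as NPWT against moist therapy over six months. The same is true of the cost-effectiveness ratio if study period means six months. The six-month SAE and mortality comparison is exposed to discretionary switching because it is grouped by treatment given.

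On the planned rates, up to 62.5% of patients could be treated outside their allocation after day 112. With constant hazards, the six-month closure difference lies between 18.2 and 4.2 points depending on those choices alone; how much switching will occur is unknown. The primary endpoints and the sample size are unaffected. A reader might infer that the six-month closure results are invalid or biased. They are not: they answer a different question from the one in the stated aim. What the article's stated windows lack is an all-cause safety contrast by arm and a cost contrast confined to the randomised treatment period.

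**What to change.** Keep the six-month analyses and the planned economic horizon, and add the following.

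1. In Primary and secondary endpoints and in Statistical analysis: a comparison of all-cause SAEs and mortality up to day 112 by randomised arm, beside the planned presentation by treatment given.
2. In Health economic evaluation and analysis: a cost-effectiveness ratio with costs and closures cut at day 112, alongside the study-period ratio and not in its place. Replacing the planned ratio would drop later costs and closures, which is a debatable trade-off and not a correction.
3. For the six-month closure results: present them as comparisons of initial strategies with free treatment choice after week 16, and show the number per arm using NPWT after day 112, where recorded.

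The cost is a few extra tables and fewer events in the day-112 comparisons. The second item needs resource use that can be split at day 112, and the third needs treatment records for weeks 17 to 26; the article does not confirm that either is collected. No change to treatment after week 16 is proposed.
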